#### Adherence

Participants will be asked to complete the MARS-5 questionnaire to assess metformin adherence [33]. If adherence is below the equivalent of 6 months over 5 years (10%) the participant will be non-evaluable. During the titration phase, metformin tolerance will be checked every 2 weeks via a telemed call by the research team based at the Oxford investigator (recruiting) site. Thereafter, adherence will be checked every 6 months via a telemed call using the MARS-5 questionnaire for the duration of the trial. Concomitant medication may be given as medically indicated.

#### Participant timeline

The participant timeline is outlined in Fig. 3.

**Fig. 3 Fig3:**
[figure not shown]
Participant flow diagram

#### Outcomes: trial end-points

##### Primary end-point

Cumulative cancer-free survival up to 5 years (60 months) from randomisation between participants in the intervention (metformin) versus control (no metformin) arms. “Cancer” event defined as pathologically confirmed diagnosis of malignant cancer identified during trial participation or death from any cause.

##### Secondary end-points

i.Comparison of cumulative tumour-free survival at 5 years between trial arms. “Tumour” event including pathologically confirmed diagnosis of malignant cancer or clinically/scan detected benign or premalignant lesion death from any cause.ii.Comparison of overall survival at 5 years between trial armsiii.Comparison of clinical characteristics of emerging cancers between trial arms.iv.Safety and toxicity of metforminv.Acceptability of metforminvi.Impact of metformin on quality of life (QOL)vii.Impact of baseline lifestyle risk factors (e.g. weight, BMI, smoking, etc.) on cancer incidence

##### Exploratory end-points

To establish the mechanism of action of metformin as a cancer-preventativei.Whether baseline insulin sensitivity (using HOMA-IR as a surrogate marker) predicts cancer-free survivalii.Proportion of metformin’s chemoprevention effects that are indirect via insulin sensitivity (using HOMA-IR as a surrogate marker)iii.Proportion of metformin’s chemoprevention effects that are indirect via changes in circulating PI3K/AKT/mTOR signalling (using change to PI3K score).iv.Proportion of metformin’s chemoprevention effects that are direct via alterations to oxidative phosphorylation using OXPHOS gene signature as a surrogate marker.To identify biomarkers of response or carcinogenesisi.Surrogate genetic and epigenetic markers of cancer-free survival or metformin response using next-generation sequencing of PBMCs and cfDNAii.Proteomic markers of cancer-free survival or metformin response using reverse phase protein array of PBMCs.iii.Penetrance of *TP53* GPV in tumour tissue, correlating GPV with cancer diagnosis (location, stage and grade).iv.Retrospective identification or validation of circulating cancer biomarkers using mass spectroscopy/ELISA of serial plasma samplesTo assess WB-MRI performance as a diagnostic tool for detecting cancers in participants with LFS by assessing yield and diagnostic accuracy of WB-MRI.

#### Sample size

Cancer incidence is affected by type and penetrance of *TP53* mutation [34] and is significantly reduced by prophylactic mastectomy. The SIGNIFY study [5] identified 13% of cancers after baseline imaging in 44 patients but, as many did not have preceding annual surveillance, this carries an inherent prevalence bias. As patients with cancers detected at baseline will be excluded from MILI, we referenced data collected between 2013 and 2017 from 1000 LFS adults by the international Li-Fraumeni Exploration (LiFE) Research Consortium [35]. These patients had undergone annual surveillance scans. This revealed an average yearly cancer incidence of 5% (unpublished). Therefore, we assume a 5% per year cancer incidence in our control arm.

The addition of metformin is estimated to reduce new cancer events by 50% at 5 years corresponding with a reduction in all-cause mortality by 20%. This assumes that 77% of participants will be cancer-free at 5 years in the control arm, and if the treatment reduces the incidence of cancer by 50%, 88.5% in the treatment arm will be cancer-free at 5 years. Were we to select a small effect size of, for example, 25%, we would need to recruit 1044 participants which would be unachievable given the LFS population and provide a median survival advantage of only 5 years in the metformin arm, equivalent to the duration of the study. Therefore we chose a higher effect size so data from this study could be used for the international meta-analysis powered to detect a lower risk reduction. This strategy was recently exemplified with pooling of data from the COVID-19 UK’s Recovery and WHO’s Solidarity trials to show the impact of hydroxychloroquine on survival [36]. The predicted median survival will be 28 years (from recruitment) in the metformin arm versus 13 years in the control arm. To detect this effect size with 80% power and one-sided log rank test with 5% error, 44 events should be observed. A sample size of 224 participants (112 in each arm) recruited over 2 years with a further 5 years of follow-up is therefore needed in order to observe this number of events with these assumptions. A 1% loss to follow-up rate and no treatment crossovers are also assumptions made.

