Due to the rarity of *TP53* GPV, the UK prevalence of LFS is too low to conduct these association studies. Hence, an international LFS consortium has been established with investigators from the National Cancer Institute (NCI, USA), Hannover (Germany) and SickKids (Canada), to conduct parallel MILI studies in the USA and Germany so that data can be pooled to address cancer penetrance. Trial centres in each nation are seeking independent funding to conduct MILI in adults and/or children using a locally adapted core protocol. Each trial will be sufficiently powered to address the primary objective as a standalone trial. Results from all studies will be pooled in an individual participant data (IPD) meta-analysis to definitively determine the benefit of metformin in preventing cancer in this high-risk participant group and address secondary and translational endpoints.

The UK LFS organisation, the George Pantziarka TP53 Trust, has also been involved with the design of MILI at a very early stage of development. In addition to outreach within the LFS community, it has provided feedback and data to support the trial and is continuing a high level of PPI activity.

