#### Retention and follow-up post-withdrawal

For those who have permanently withdrawn from active trial participation early (not due to a cancer diagnosis), the investigator site will follow up on the participant’s health status with the local clinical team annually where possible for up to 5 years or until the trial ends (whichever comes first).

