**Table Taba:**

Call or visit	Window
Telemed call week 1	Within 3 working days of randomisation
Telemed call (dose titration phase)	Metformin start date + week 3/5/7/9 + within 3 working days
Telemed call months 6-60	+/- 1 week
Annual visit to investigator site	+/- 4 weeks

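### The planned 44 events count participants for 5 to 7 years, but the primary endpoint stops at 60 months, where 224 participants give about 38 expected events and about 75% power

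*Protocol article*

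**What the plan says.** The Sample size section assumes that "77% of participants will be cancer-free at 5 years in the control arm", against 88.5% with metformin. It continues: "To detect this effect size with 80% power" and a "one-sided log rank test with 5% error, 44 events should be observed". From this it concludes: "A sample size of 224 participants (112 in each arm) recruited over 2 years with a further 5 years of follow-up is therefore needed". It also assumes a 1% loss to follow-up, without giving the period, and no crossover.

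The Primary end-point section defines the outcome as "Cumulative cancer-free survival up to 5 years (60 months) from randomisation", with an event being a pathologically confirmed cancer or death from any cause. The abstract gives the same 60-month horizon. The Intervention section limits metformin to 5 years.

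The section on the international consortium says: "Each trial will be sufficiently powered to address the primary objective as a standalone trial".

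**The concern.** Recruiting over 2 years and then following for a further 5 gives the first participant 7 years of observation and the last one 5. An endpoint that ends 60 months after each person's randomisation uses none of the time beyond year 5. If the 44 events include those later years, the endpoint as written yields fewer events than the power statement needs. At stake are the stated 80% power, the standalone-power claim, and whether a cancer found in an early recruit after month 60 counts in the primary analysis. That last point should be settled before data accrue.

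**Working it through.** **Inputs (Sample size section).** Event-free at 5 years: 77% control, 88.5% metformin. 112 per arm. One-sided 5% log-rank test, 80% power. Accrual 2 years, then a further 5. Loss 1%, period not stated, so three readings are tried: none, 1% in total, and 1% per year. The cancer-free rates are taken as event-free rates for the endpoint, because no separate death rate is given.

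**Step 1: hazards.** With exponential times, λ = −ln(S)/5.
- Control: −ln(0.77)/5 = 0.0523 per year, median 13.3 years.
- Metformin: −ln(0.885)/5 = 0.0244 per year, median 28.4 years.
- Hazard ratio = ln(0.885)/ln(0.77) = 0.467.

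The medians match the plan's 13 and 28 years, so this is the model that was used.

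**Step 2: required events.** Schoenfeld: 4(1.645 + 0.842)²/(ln 0.467)² = 42.8. Freedman's formula gives 46.9. The stated 44 lies between them and is not in dispute.

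**Step 3: reproduce 224.** With loss hazard η, the chance of an observed event within T years is λ/(λ+η) × [1 − exp(−(λ+η)T)], averaged over T uniform on 5 to 7 years.

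| Loss assumption | Events from 224, 5–7 years | N for 44 events |
|---|---|---|
| none | 45.4 | 217 |
| 1% in total | 45.1 | 218.5 |
| 1% per year | 44.1 | 223.6, so 224 |

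The plan's second sample size supports the same reading. For a 25% reduction (82.75% event-free, hazard ratio 0.724, 239 events), this model with 1% loss per year needs about 1,042 participants, against 1,044 stated. With a 60-month cap it would need about 1,216.

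**Step 4: apply the 60-month endpoint.** Without loss, no survival model is needed: 112 × 0.23 + 112 × 0.115 = 25.8 + 12.9 = 38.6 events. Schoenfeld power is Φ(√d × |ln 0.467|/2 − 1.645).

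| Loss assumption | Events by month 60 | Power | N for 44 events |
|---|---|---|---|
| none | 38.6 | 76.4% | 255 |
| 1% in total | 38.5 | 76.2% | 256 |
| 1% per year | 37.7 | 75.5% | 261 |

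At the 44.1 events of the 5-to-7-year design, the same formula gives 81.1%. A log-rank simulation with 1% loss per year gives about 74% with the cap and about 79% with 5 to 7 years.

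**Step 5: what 224 can detect by month 60.** Setting 80% power at about 38 events gives |ln HR| = 2 × (1.645 + 0.842)/√38 = 0.807, a hazard ratio of about 0.445. That corresponds to 77% against about 89% event-free (0.77^0.445 = 0.89).

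**Step 6: counting years 5 to 7 instead.** Metformin stops by year 5, so those years are off treatment. About 80% power is recovered only if the hazard ratio of 0.467 persists. If the metformin-arm hazard returned to the control rate at month 60, a worst-case assumption, simulation gives about 46.5 events but only about 66% power.

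**The case against.** Five points can be made for the plan.

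- **The follow-up phrase could mean exactly 5 years each.** This does not help: 224 participants then give about 38 events, and the 44 is unsupported.
- **The analysis section sets no 60-month censoring rule for the Cox model,** and the rule may sit in documents not shown. This is fair as far as it goes. But the endpoint is printed with a 60-month limit, and no later document can make both that limit and the 44 events true on these assumptions.
- **Other 60-month passages prove little.** A reader might take "Telemed call months 6-60" or the rule for follow-up "annually where possible for up to 5 years or until the trial ends (whichever comes first" as showing that all observation stops at month 60. They do not. After titration the calls check adherence by questionnaire, and the second rule covers only people who withdrew early. Treatment duration does not fix follow-up duration either. The conflict lies between the Sample size and Primary end-point sections.
- **The shortfall is in expectation.** A reader might infer that 44 events cannot occur, or that the analysis would never be triggered. By simulation, 44 or more events by month 60 have a probability of about 15–19%, and nothing in the article makes the analysis event-driven.
- **The calculation is approximate.** Deaths without cancer would add events and might dilute the hazard ratio. The primary analysis is an adjusted Cox model, whose power is not computed here. Both caveats stand, but the plan's own power statement rests on the same simplifications.

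**Conclusion.** The sample-size arithmetic is internally sound, but it belongs to a longer observation window than the primary endpoint allows. For the endpoint as defined, 224 participants give about 38 expected events (37.7 to 38.6) rather than 44, and about 74–76% power rather than 80%. The standalone-power claim fails to the same extent. This rests on the plan's 5-year rates being the event-free rates for the endpoint, and on an unadjusted one-sided 5% log-rank test. The loss assumption makes little difference.

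A stronger conclusion, that the trial or its analysis is invalid, is not supported. The error rate, the endpoint and the method are unaffected, and the loss is about 5 percentage points of power. The article also says that the rare population limits recruitment and that the data are meant for a pooled analysis. This should be fixed, but it does not threaten the design.

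**What to change.** Make the Primary end-point and Sample size sections agree.

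**Simplest route.** Keep the 60-month endpoint. Restate the planning figures as about 38 expected events and about 75% power at a hazard ratio of 0.467, or as 80% power for a hazard ratio of about 0.445. State the period to which the 1% loss applies. Amend the standalone-power sentence in the consortium section to match. This changes wording only, at the price of a less favourable stated power.

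**If the sponsor means to count all follow-up to a common close.** The endpoint definition must say so, and cancer and vital status must be collected past month 60 for early recruits (0 to 2 further years, largely from routine annual surveillance). Power must then be recomputed under a stated assumption about the effect after treatment ends, between about 80% if the hazard ratio persists and about 66% if the hazard returns to the control rate. This costs more than wording: it needs an amendment, it adds data collection, and it changes what the primary comparison estimates.

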### Assignment of interventions

#### Allocation

Participants are randomised 1:1 to one of two groups: surveillance plus metformin or surveillance alone. The control arm of surveillance alone without metformin (rather than surveillance plus placebo) was decided following a consultation and survey carried amongst the LFS community. Randomisation will be undertaken using minimisation, with minimisation factors: sex, age (16–25/26–35/36–45/46+ years), prior cancer, prior bilateral mastectomy and de novo versus familial mutTP53. The minimisation algorithm will be seeded with the initial participants using simple randomisation. A probabilistic element is included so minimisation is non-deterministic.

#### Implementation

Investigator (recruiting) site staff will confirm the diagnosis and the participant’s eligibility by completing the eligibility checklist within the trial randomisation form and randomising them to one of the two arms in the REDCap clinical trial database.

### Data collection, management and analyses

#### Data collection plan

In addition to baseline imaging and screening tests, all MILI participants undergo annual evaluation of fasting glucose and insulin levels to determine their insulin sensitivity (using the HOMA-IR score). Peripheral blood mononuclear cells (PBMCs) will be collected for next-generation sequencing of metabolic genes alongside proteomic measurement of PI3K/mTOR activity using reserve phase protein array (RPPA). Longitudinal plasma and cell-free DNA samples will also be collected so that carcinogenesis biomarkers can be retrospectively identified in those developing cancers during the study. In addition, tumour tissue will be sequenced to characterise *TP53* mutations and other relevant genetic changes. See Appendix Table 2 for full summary schedule of events.

Consent includes permission to conduct ancillary research on samples collected during the study. Researchers wishing to conduct appropriate and relevant research on the samples obtained during the study can request permission to access them via the Sample Access Committee which will be convened during the study.

#### Retention and follow-up post-withdrawal

For those who have permanently withdrawn from active trial participation early (not due to a cancer diagnosis), the investigator site will follow up on the participant’s health status with the local clinical team annually where possible for up to 5 years or until the trial ends (whichever comes first).

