#### Statistical analysis

A detailed statistical analysis plan (SAP) has been drafted prior to the trial opening and will be finalised in advance of any primary outcome analysis. This plan will be reviewed by and receive input from the trial team and external committees (e.g. Data Safety Monitoring Committee) if appropriate.

All analyses will be on an intention-to-treat basis. Initial data analysis will be performed without knowledge of the randomisation status of participants. This means that participants will be analysed as they are randomised irrespective of the treatment actually received. Further sensitivity analysis populations will be defined in the SAP. Numerical and graphical summaries of all data will be presented including descriptions of missing data at each level. Kaplan-Meier curves will be produced by the intervention group for time-to-event outcomes.

Estimates of treatment effects will be reported with 95% CIs. The primary outcome will be analysed using a Cox proportional hazards regression model, with time-to-cancer event as the outcome; allocated group will be included as a covariate, as well as the minimisation factors (sex, age in years, prior cancer, prior bilateral mastectomy, de novo versus familial mutTP53). The proportional hazards assumption will be assessed graphically.

Details of secondary outcome analysis methods will be fully defined in the SAP but time-to-event outcomes will be analysed using the same principles as defined for the primary outcome.

A subgroup analysis of participants with de novo versus familial *TP53* GPV will be conducted as part of the MILI trial analysis. Pooled international analyses will be conducted after the completion of MILI as part of a separate trial.

Missing data will be minimised by careful data management. Missing data will be described with reasons given where available. The number and percentage of individuals in the missing category will be presented by treatment arm. All data collected in the electronic data capture system will be used, since only essential data items will be collected. No data will be considered spurious in the analysis since all data will be checked and cleaned before analysis. Analysis of exploratory end points may be performed separately from the final analysis as performed by the trial statisticians in accordance with the SAP.

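### The only stated follow-up after leaving the trial excludes those who leave because of cancer, which does not fit a 5-year overall survival comparison by intention to treat

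*Protocol article*

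**What the plan says.** The protocol article's section Retention and follow-up post-withdrawal defines who is followed after leaving active participation: "For those who have permanently withdrawn from active trial participation early (not due to a cancer diagnosis), the investigator site will follow up". That follow-up asks the local clinical team about health status, "annually where possible for up to 5 years or until the trial ends (whichever comes first"). It is the only provision for follow-up after leaving in the available text.

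Three other places bear on it:

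- Secondary end-points, item ii, compares overall survival at 5 years between the arms. The Background section on precision-prevention trials also lists overall survival among the outcomes used to judge whether metformin works.
- Statistical analysis states: "All analyses will be on an intention-to-treat basis". Participants are analysed in the arm to which they were randomised.
- Sample size links the assumed cancer effect to mortality: "corresponding with a reduction in all-cause mortality by 20"%.

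The primary event is a "pathologically confirmed diagnosis of malignant cancer identified during trial participation or death from any cause".

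**The concern.** The parenthesis implies that a cancer diagnosis can be the reason for leaving active participation, and it places those participants outside the annual status check. For the primary endpoint this does no harm, because the cancer has already been counted. For overall survival it matters, because a cancer diagnosis is when the risk of death would be expected to rise.

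If observation ends there, the censoring depends on prognosis. Survival would be overstated in both arms, and more so in the arm with more cancers. Under the trial's hypothesis that is the control arm, so a true mortality benefit would be diluted. An analysis plan cannot repair this later, because it can only use data that were collected. The planned individual participant data meta-analysis would inherit the same gap in any survival analysis.

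**Working it through.** **1. The plan's own design figures.** Inputs from Sample size: "77% of participants will be cancer-free at 5 years in the control arm", "88.5% in the treatment arm will be cancer-free at 5 years", and "To detect this effect size with 80% power and one-sided log rank test with 5% error, 44 events should be observed".

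- Hazard ratio = ln(0.885)/ln(0.77) = 0.467.
- Events (Schoenfeld, 1:1) = 4 × (1.645 + 0.842)² / (ln 0.467)² ≈ 42.8, so 43. The plan states 44.
- Hazards: control −ln(0.77)/5 = 0.0523 per year; metformin −ln(0.885)/5 = 0.0244 per year. Medians are 13.3 and 28.4 years; the plan states 13 and 28.
- With uniform accrual over 2 years and 5 to 7 years of follow-up, 224 participants give 45.4 expected events with no loss, or 44.1 with 1% loss per year.

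The design figures reproduce. They concern cancer-free survival and do not depend on what happens after a cancer.

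**2. How many participants the exclusion could touch.** First events by 60 months:

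- Control: 112 × 0.23 = 25.8
- Metformin: 112 × 0.115 = 12.9
- Total: 38.6, about 39, or 38.6/224 = 17% of participants

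This is an upper bound. The endpoint also counts deaths, and the text does not say that everyone leaves at diagnosis.

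**3. How much observation time that is.** With hazard λ, person-years between the first event and 60 months are 112 × [5 − (1 − e^(−5λ))/λ].

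- Control: 112 × (5 − 0.23/0.0523) ≈ 67 of 560
- Metformin: 112 × (5 − 0.115/0.0244) ≈ 33 of 560

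**4. How many deaths could fall in that time.** The documents give no mortality after cancer, so a constant rate m, equal in both arms, is assumed and varied. Treating every first event as a cancer followed by leaving:

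deaths = 112 × ∫₀⁵ λe^(−λt) [1 − e^(−m(5−t))] dt

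| Assumed m per year | Control | Metformin | Total |
|---|---|---|---|
| 5% | 3.1 | 1.5 | 4.6 |
| 10% | 5.7 | 2.8 | 8.5 |
| 20% | 9.8 | 4.8 | 14.6 |
| 30% | 12.8 | 6.3 | 19.1 |

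The total runs from about 5 to about 19, with a control-to-metformin ratio close to 2:1 throughout.

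**The case against.** The strongest reply is that the section only sets a route for one group. It does not say that participants with cancer are no longer followed, and no part of the article sets a censoring rule for overall survival. A cancer diagnosis is the primary event, so the parenthesis may simply separate true withdrawals from participants who have reached the endpoint and are handled elsewhere. The participant flow diagram (Fig. 3), the full schedule of events (Appendix Table 2) and the full protocol are not visible here, and any of them could hold that route. The article also plans to describe emerging cancers and sequence tumour tissue, so some contact after diagnosis is expected, although neither activity establishes vital-status follow-up.

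Much of this stands. A reader might infer that the trial will miss the deaths overall survival is meant to count, or that most deaths in the trial would be lost. The documents support neither. Deaths without a prior cancer, deaths after withdrawal for other reasons, and deaths in participants who stay in the trial after cancer would still be counted. No figure in the documents gives the share of deaths that follow a cancer. Overall survival also has no stated power or event target, and the 20% mortality figure accompanies the cancer assumption without driving the sample size.

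The reply does not remove the explicit exclusion. This is more than a detail that a condensed article leaves out: the article states a follow-up rule and carves out the group that matters most for overall survival.

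**Conclusion.** The point holds conditionally. As written, the follow-up rule conflicts with a 5-year overall survival comparison by intention to treat, which needs vital status for everyone randomised. If the full protocol has no other route, overall survival would be informatively and unequally censored.

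The exposure is at most the 39 or so participants with a first event by 60 months. The range of 5 to 19 uncounted deaths rests on three assumptions: that all these events are cancers, that all those participants leave, and that mortality after cancer is 5 to 30% per year. The direction, towards diluting a benefit, further assumes that metformin does reduce cancers. If another route does exist, what remains is a wording conflict between two sections. Either way the primary endpoint, the 44 events and the 224 participants stand.

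**What to change.** In Retention and follow-up post-withdrawal, delete the parenthesis. Alternatively, state there that vital status, with date and cause of death, is obtained annually for all randomised participants, including after a cancer diagnosis, to 60 months or trial end, so that a cancer diagnosis does not end overall survival follow-up. If the full protocol already provides this, a cross-reference is enough.

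The cost is one status query a year to the local clinical team for each affected participant, about 39 people at most, through the channel already planned for other withdrawals. Treatment, visits and sample size do not change.
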